### Randomization

Participants are individually randomized to placebo or probiotics groups in a 1:1 allocation. Random number are generated by excel and overseen by an independent statistician. Research staff and participants remain blind to the allocated treatment group.

### Statistical methods

All analyses of end points are based on the intention-to-treat (ITT) principle. The results of the trial are reported as comparative summary statistics (difference in response rate or means) with 95 % confidence intervals. All statistical tests use a 5 % with two-sided significance level. Two-sided *t*-tests and chi-square tests are used to analyze the differences between the groups at baseline and during follow-up. For the primary outcome, survival curves are used to calculate the cumulative incidence of diabetes. The difference between the groups in the incidence of diabetes is tested by means of the two-sided log-rank test. For the secondary outcomes (the difference of the changes of blood glucose, lipid profile and insulin sensitivity, body weight, waist circumference, abundance of bacteria, levels of LPS and GLP-1 between the two groups), a mixed models are used on data collected at 6,12,18 and 24 months. An interaction between treatment group and time is fitted to allow estimation of treatment effects at each time point. The model adjusts for baseline variable and minimization factors. Linear Pearson’s correlation, partial correlation, and logistic regression analysis are used for analyzing relationships.

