#### Secondary outcomes

(i) the cumulative prevalence of diabetes in the two groups, (ii) the changes of blood glucose, lipid profile and insulin sensitivity in the two groups, (iii) the changes of body weight and waist circumference, (iv) the safety assessment of probiotics, (v) the change of the abundance of gut bacteria, (vi) the change of blood lipopolysaccharides (LPS) and GLP-1 levels.

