#### Follow-up visits

The purpose of follow-up visits is to monitor the compliance and to discover the adverse events. After the first visit, a researcher will contact participants every month to check their medication. The participants will have follow-up visits to the clinical laboratory every 2 months. Their height, weight, waist circumference, hip circumference, blood pressure, heart rate and newly combined medication will be checked at those time points. In addition, at months 6, 12, 18, 24, participants will undergo a 75 g OGTT to evaluate the glycemic status (blood draw after 8 h overnight fasting and 30 min and 2 h after glucose load) and take blood samples and fecal samples (Table 1).

**Table 1 Tab1:** Visit study and efficacy variables for Probiotics Prevention Diabetes Programme (PPDP)

Visit number	1	2	3	4	5	6	7	8	9	10	11	12	13
Study month	0	2 m	4 m	6 m	8 m	10 m	12 m	14 m	16 m	18 m	20 m	22 m	24 m
Newly diagnosed diabetes(*n*)	×			×			×			×			×
OGTT + IRT(0 min,30 min,2 h)^a^	×			×			×			×			×
Total cholesterol	×			×			×			×			×
Triglyceride	×			×			×			×			×
High-density lipoprotein	×			×			×			×			×
Low-density lipoprotein	×			×			×			×			×
Body weight	×	×	×	×	×	×	×	×	×	×	×	×	×
Systolic blood pressure	×	×	×	×	×	×	×	×	×	×	×	×	×
Diastolic blood pressure	×	×	×	×	×	×	×	×	×	×	×	×	×
Waist circumference	×	×	×	×	×	×	×	×	×	×	×	×	×
Hip circumference	×			×			×			×			×
Abundance of bacteria	×			×			×			×			×
LPS	×			×			×			×			×
GLP-1	×			×			×			×			×

^a^OGTT, oral glucose tolerance test; IRT, insulin release test; LPS, lipopolysaccharides

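### Body weight and waist are scheduled at 12 follow-up visits, but their mixed model uses only four; using all 12 is a cheap, minor improvement, not the correction of an error

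*Protocol article*

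**What the plan says.** The Secondary outcomes section lists "the changes of body weight and waist circumference" as item (iii). Under Follow-up visits, "The participants will have follow-up visits to the clinical laboratory every 2 months", and of those visits it says: "Their height, weight, waist circumference, hip circumference, blood pressure, heart rate and newly combined medication will be checked at those time points". Table 1, whose caption refers to efficacy variables, agrees for these two outcomes: it marks body weight and waist circumference at month 0 and at every two-monthly visit to month 24.

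The glucose tolerance test and the blood and stool samples follow a sparser schedule: "at months 6, 12, 18, 24, participants will undergo a 75 g OGTT to evaluate the glycemic status". Table 1 places lipids, bacterial abundance, LPS and GLP-1 at those same months.

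The Statistical methods section then lists the secondary outcomes in one sentence, naming body weight and waist circumference among them, and says that "a mixed models are used on data collected at 6,12,18 and 24 months". It adds: "An interaction between treatment group and time is fitted to allow estimation of treatment effects at each time point". The model adjusts for baseline.

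**The concern.** The six-monthly grid is the only one possible for glucose, lipids, insulin sensitivity, bacteria, LPS and GLP-1, because those are not measured at other follow-up visits. Weight and waist are. The article extends the grid to them without giving a reason, and because the four months are stated outright, the choice can be reviewed as written.

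Three things are at stake, all for two secondary outcomes:

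- A participant seen at month 2, or at months 2 and 4, who leaves before month 6 has follow-up weight and waist on record, but none of it enters the model.
- A likelihood-based mixed model with incomplete data is valid if missingness depends only on values in the model. If someone stops after an unfavourable weight at, say, month 16 or 22, that value is outside the model and the assumption is harder to defend.
- The model gives no estimate of change before month 6. The Background section argues that trials of 4 to 8 weeks may have been too short to show an effect. Months 2 and 4 are this trial's own data on early change in weight and waist.

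**Working it through.** **1. Count of measurements (Table 1 against Statistical methods).** Follow-up visits: months 2, 4, …, 24, so 24/2 = 12. Modelled: 6, 12, 18, 24, so 4. Not modelled: 2, 4, 8, 10, 14, 16, 20, 22, so 8. Share not modelled: 8/12 = 67%.

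**2. Precision of the planned contrasts.** The plan estimates a treatment effect at each time point. With complete data, and baseline adjustment free to differ by visit, every visit has the same regressors, so generalised least squares reduces to a separate baseline-adjusted comparison at each visit. Adding visits then changes nothing: the variance ratio (4-visit model over 12-visit model) at month 24 is 1.000.

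With dropout, the information matrix is the sum over dropout patterns of *w X′Σ⁻¹X*, where *w* is the share of participants with that pattern. The 10% dropout comes from Sample size calculations. The following are assumed, not in the documents: monotone dropout spread evenly over the 12 intervals, four correlation structures, and correlation parameters of 0.5, 0.7 and 0.9 (at a six-month lag for the autoregressive forms). Variance ratios for the month-24 effect:

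| Correlation structure | 10% dropout (0.5 / 0.7 / 0.9) | 30% dropout, assumed (0.5 / 0.7 / 0.9) |
|---|---|---|
| Exchangeable | 1.0095 / 1.0115 / 1.0129 | 1.0296 / 1.0360 / 1.0404 |
| Autoregressive | 1.0064 / 1.0076 / 1.0085 | 1.0237 / 1.0277 / 1.0300 |
| Half constant, half autoregressive | 1.0074 / 1.0080 / 1.0086 | 1.0265 / 1.0287 / 1.0302 |
| Autoregressive plus noise | 1.0053 / 1.0065 / 1.0080 | 1.0195 / 1.0233 / 1.0275 |

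The four-visit model therefore loses 0.5% to 1.3% of variance at the plan's dropout, and 2.0% to 4.0% at 30%. Repeating the check at months 6, 12 and 18 gave no loss larger than the month-24 one.

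**3. Precision of an average over follow-up (not in the plan).** With exchangeable correlation *r*, the baseline-adjusted variance of the mean of *k* visits, in units of the outcome variance, is (1 + (*k* − 1)*r*)/*k* − *r*².

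- *r* = 0.6: *k* = 4 gives 0.700 − 0.360 = 0.340; *k* = 12 gives 0.633 − 0.360 = 0.273; reduction 19.6%.
- *r* = 0.7: 0.775 − 0.490 = 0.285; 0.725 − 0.490 = 0.235; reduction 17.5%.
- *r* = 0.9: 0.925 − 0.810 = 0.115; 0.908 − 0.810 = 0.098; reduction 14.5%.

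**4. Participants with no modelled follow-up value although measured.** With 10% dropout over 24 months at constant hazard, the proportion remaining at month *t* is 0.9^(*t*/24). Leaving between months 2 and 6: 0.9^(2/24) − 0.9^(6/24) = 0.9913 − 0.9740 = 0.0173. Times 220 enrolled: 3.8, so about 4 people.

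**5. Size of the larger model.** An unstructured covariance matrix for *k* visits has *k*(*k* + 1)/2 parameters: 4 × 5/2 = 10 for four visits, 12 × 13/2 = 78 for twelve.

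**The case against.** The case for leaving the plan alone is strong, and most of it stands. A common six-monthly grid is a clear prespecified choice, no two parts of the article contradict each other, and measuring a variable more often than it is modelled is ordinary practice. The article gives a monitoring reason for the visits: "The purpose of follow-up visits is to monitor the compliance and to discover the adverse events". That reason is not exclusive, though, since Table 1 presents weight and waist at every visit as efficacy variables.

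A reader might infer from the 67% that the plan throws away most of its precision. It does not: the planned contrasts are specific to each time point, and step 2 puts the loss at zero to about 1%. The 14% to 20% in step 3 belongs to an average that the plan does not define. An average over months 2 to 24 also covers a different period from one over months 6 to 24, so the two share a target only if the effect is constant over time.

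A reader might also infer a breach of the stated intention-to-treat principle. That is not supported. A fixed assessment grid reassigns nobody and excludes nobody for treatment received or adherence. Someone who leaves before month 6 has no value at months 6 to 24 under either model; months 2 and 4 would inform those contrasts only indirectly, through their correlation with later visits.

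Finally, the article plans t-tests and chi-square tests of group differences during follow-up without limiting them to four months, so the interim data cannot be called discarded outright. But that sentence names neither outcome nor month, and it does not replace the baseline-adjusted model that the article assigns to weight and waist by name.

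**Conclusion.** The point holds as a minor improvement to the analysis of two secondary outcomes. The count is certain: 8 of 12 scheduled follow-up measurements of weight and waist do not enter their model. The cost in precision is negligible for what the plan estimates. What remains is about 4 of 220 participants with measured but unmodelled follow-up, a weaker basis for missing-at-random, and no modelled estimate of change before month 6, although no listed outcome asks specifically for early change. The primary outcome is unaffected.

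The variance figures rest on the assumed correlations and evenly spread monotone dropout, and the headcount on constant-hazard dropout at the plan's 10%. The benefit for missing-at-random is a matter of reasoning and was not quantified.

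**What to change.** In Statistical methods, state that the models for body weight and waist circumference use all scheduled post-baseline visits (months 2 to 24), with the baseline value and a treatment-by-time interaction. Keep the month 6, 12, 18 and 24 contrasts as the reported estimates, and keep the four-month grid for variables measured only then. An average effect over follow-up may be added as an optional summary, with its months and weighting defined.

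This costs about one sentence and no new visits, since the measurements are already scheduled. The downside is the larger covariance matrix: 78 unstructured parameters may not be estimated stably with about 200 participants, so name a structured covariance in advance as the fallback.

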**Methods/Design:**

A 24-month randomized intervention is conducted from January 2014 to December 2016. The target sample size for intervention is 200 middle-aged men and women aged 30–65 year-old with impaired glucose tolerance. Participants with persistent impaired glucose tolerance were assigned to group A (tablet A) and B (tablet B) in sequential order. The participants and investigators were blinded to the assignment. The primary outcome is development of diabetes. The secondary outcome measures include body composition, biochemical variables and the safety of the probiotics.

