## Methods/Design

### Trial design

The PPDP is a 24-month, double-blinded, two-arm parallel group trial. Participants are individually randomized to one of two intervention groups in a 1:1 allocation. Participants are recruited from the outpatient department of five clinical centers in Shanghai during 2014 to 2016. They are Shanghai East Hospital, Shanghai Fifth People’s Hospital, Xinhua Hospital, Chongming Branch, Shanghai Pudong Hospital, Shanghai Seventh People’s Hospital. After an initial screening, potential subjects will be assessed for inclusion in the run-in trial. Those who meet the inclusion criteria are randomized to either intervention group or placebo group (Fig. 1).

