### Trial procedures

#### Screening

The purpose of the screening is to verify the eligibility of potential participants selected from the Department of Outpatient. The recruitment of participants will be done in the Department of Endocrinology of Shanghai East Hospital, Shanghai, China. Every potential participant will be informed the detailed information of the objectives of the study, the participated risks and the expected benefits. When the concert form has been signed, participants will be asked to fill a standardized questionnaire about medical history and to undergo a 75 g OGTT, insulin release test, liver and kidney function test (blood draw after 8 h overnight fasting and 30 min and 2 h after glucose load).

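### The secondary-outcome mixed model adjusts for minimisation factors that the described allocation does not have; adjusting the primary comparison for baseline 2-h glucose is an optional gain

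*Protocol article*

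**What the plan says.** **Adjustment set.** In the protocol article, Statistical methods assigns mixed models to the secondary outcomes (glucose, lipids, insulin sensitivity, weight, waist, gut bacteria, LPS, GLP-1) and then states: "The model adjusts for baseline variable and minimization factors". The factors are not named.

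**Allocation.** The Randomization section says "Participants are individually randomized to placebo or probiotics groups in a 1:1 allocation" and "Random number are generated by excel and overseen by an independent statistician". The Abstract says that participants "were assigned to group A (tablet A) and B (tablet B) in sequential order". No section describes minimisation or stratification.

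**Primary test.** Statistical methods says: "The difference between the groups in the incidence of diabetes is tested by means of the two-sided log-rank test". It states no covariate or stratum. Follow-up visits provides that "at months 6, 12, 18, 24, participants will undergo a 75 g OGTT to evaluate the glycemic status", and Table 1 also schedules an OGTT at month 0, so baseline 2-h glucose is available for everyone. Entry requires it to lie between 7.8 and just under 11.1 mmol/L.

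**Centres.** Trial design says "Participants are recruited from the outpatient department of five clinical centers in Shanghai during 2014 to 2016", whereas Screening says "The recruitment of participants will be done in the Department of Endocrinology of Shanghai East Hospital, Shanghai, China".

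**The concern.** Minimisation factors exist only if a minimisation scheme was used. The article describes the allocation and the adjustment set a few lines apart, and they do not fit together. A reader cannot tell whether the Randomization section leaves out a scheme or the Statistical methods section carries a term that does not belong to this trial.

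At stake is prespecification of every continuous secondary result. If the covariates are settled only once data are in, they can be chosen with the results in view. Holding the treatment key with a third party gives partial protection only, because results can still be compared as tablet A against tablet B. If minimisation was in fact used, the allocation is misdescribed, and the primary test omits the balancing factors that the secondary models include.

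A second, lesser matter is efficiency. Diabetes is diagnosed largely by a rise in 2-h glucose, so its baseline value is plausibly prognostic, and the primary comparison does not use it.

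**Working it through.** **1. The sections side by side**

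| Section | What it implies | Balancing factors named |
|---|---|---|
| Abstract | assignment in sequence | none |
| Randomization | Excel random numbers, 1:1 | none |
| Statistical methods | minimisation was used | none |

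Neither the Abstract nor the Randomization section describes minimisation. With no factor named anywhere, the model's covariate list cannot be written down from the article.

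**2. The plan's own power figure**

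Inputs from Sample size calculations: 100 per arm, 35% on placebo, a 14-point difference (so 21%), two-sided 0.05, 80% power.

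- Required n per arm = [1.960·√(2·0.28·0.72) + 0.842·√(0.35·0.65 + 0.21·0.79)]² / 0.14² ≈ 160.3, so 161. The stated 100 does not reproduce.
- Power at 100 per arm = Φ[(0.14·√100 − 1.960·0.635)/0.627] = Φ(0.248) = 60%.
- Log-rank: HR = ln 0.79 / ln 0.65 = 0.547; events = 35 + 21 = 56; power = Φ(√56/2 · |ln 0.547| − 1.960) = Φ(0.296) = 62%.

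The baseline for any gain is therefore about 60%, not 80%. That shortfall is a separate matter.

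**3. What adjustment for baseline 2-h glucose could add**

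Model: hazard = exp(λ + βx), with x standard normal and β = ln(HR per SD). In each arm λ is set so that the marginal 2-year rate is 35% or 21%. Events are read at 6, 12, 18 and 24 months; 100 per arm; no dropout. **The HR per SD is an assumption**, because the article links neither baseline 2-h glucose nor centre to conversion.

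- Simulation A: complementary log-log model without and with x; 800 trials per setting, Monte Carlo SE about 1.7 points.
- Simulation B: plain log-rank against Cox with Efron ties and x, likelihood-ratio test; 1,500 trials per setting, SE about 1.3 points.

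| HR per SD | A: power % | A: gain | B: power % | B: gain |
|---|---|---|---|---|
| 1.0 | not run | – | 60.7 → 61.2 | 0.5 |
| 1.3 | not run | – | 59.5 → 59.8 | 0.3 |
| 1.5 | 61.3 → 63.9 | 2.6 | 60.5 → 64.0 | 3.5 |
| 2.0 | 61.8 → 67.8 | 6.0 | 59.4 → 66.6 | 7.2 |
| 2.5 | 63.0 → 75.0 | 12.0 | 63.0 → 73.3 | 10.3 |

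**4. Side checks**

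- *Validity.* With no treatment effect, the unadjusted log-rank rejected in 5.1% and 5.4% of trials in simulation B, close to the nominal 5%.
- *Centre.* A log-rank stratified by five centres, with no centre effect, had power 0 to 2 points below the plain log-rank.
- *Ties.* With only four event times, the handling of ties matters. A further run (2,000 trials per setting) used Cox with Breslow ties and a Wald test. Against the log-rank it fell from 60.7% to 56.1% at HR 1.0 and from 59.6% to 56.9% at HR 1.5, and rose only from 60.3% to 65.8% at HR 2.5. Efron ties with a Wald test were within 1 point of the log-rank at HR 1.0 and 1.3. The statement that adjustment costs nothing therefore holds for the complementary log-log model or Efron ties, not for every Cox implementation.

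**The case against.** The mismatch is one term, and it touches only the secondary model. A condensed article need not list balancing factors, and an analysis plan that is not shown may name them. That limits the consequence: the article does not show that factors were, or will be, chosen after the data are seen, nor that minimisation was not used. It does not remove the contradiction, because the article describes the allocation and describes it as something else.

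On the primary test the opposing case largely succeeds. A reader might infer any of the following, and the documents do not support them:

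- *The unadjusted log-rank is an error.* It is a standard test and holds its level. Its type I error already allows for chance imbalance in baseline glucose.
- *It certainly loses power.* The loss depends on a prognostic strength that the article does not give and is nil at the weak end. The simulations also used an untruncated normal covariate, whereas the entry limits restrict the spread of 2-h glucose, which makes the strongest values harder to reach.
- *Leaving out centre loses power.* Nothing shows a centre effect, stratification gained nothing when there was none, and the article is unclear whether recruitment is at five centres or one.
- *The reporting ignores censoring.* The sentence on differences in response rates is a general one for all endpoints. For the primary outcome the same section uses survival curves to obtain cumulative incidence.
- *Reading conversion at four visits is a fault.* Both arms follow the same schedule, and no bias was shown. The grouping matters only for how ties are handled if a Cox model is adopted.

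**Conclusion.** The contradiction stands. The secondary mixed model refers to minimisation factors, the described allocation has none, and the model cannot be run from the article as written. This rests on the text alone and has no numerical size. Which of the two sections is wrong cannot be told from the article.

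Adjusting the primary comparison for baseline 2-h glucose is an improvement, not the correction of an error. At 100 per arm and 35% versus 21%, it is worth 0 to 1 point of power at HR 1.0 to 1.3 per SD, about 3 at 1.5, 6 to 7 at 2.0 and 10 to 12 at 2.5. These figures assume proportional hazards, no dropout, and either a complementary log-log model or Efron ties. The best case tried reaches 75%, so adjustment does not make up for the sample size.

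**What to change.** **Needed, before unblinding.** The sponsor should confirm how allocation was done and make the two sections agree:

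- if minimisation was used, describe the scheme and its factors under Randomization and use those factors in the analysis;
- if not, delete the term and adjust each secondary model for the baseline value of its own outcome only. Add centre only if allocation was in fact stratified by centre.

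Cost: a sentence or two, and no new data.

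**Recommended.** Prespecify the primary treatment comparison as a model for time to first diabetes adjusted for baseline 2-h glucose: complementary log-log on the four visit intervals, or Cox with Efron ties and a likelihood-ratio test, two-sided 5%. Keep the unadjusted log-rank test and Kaplan-Meier curves as supportive. The adjusted hazard ratio is conditional on baseline glucose and need not equal the unadjusted one, so label it as such. The data are already scheduled, but this changes the primary analysis after recruitment has begun, so it needs a dated amendment made while the treatment key is still held by the third party and before any comparison of tablet A with tablet B.

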### Reporting of adverse events for this trial

We will report adverse events that might be reasonably related to probiotics. Adverse events are collected from time of signature of informed consent throughout the treatment period.

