## Abstract

**Background:**

Alterations in intestinal microbiota correlate with risk of development of obesity and type 2 diabetes. Probiotics have been suggested to play an important role in the management of dysglycemia, although the evidence is limited. In this study, we aim to explore the efficacy and safety of probiotics intervention in preventing type 2 diabetes in Chinese patients with impaired glucose tolerance.

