Recent evidences suggest that alterations in gut microbiota play an important role in the pathogenesis of obesity-related disorders, including diabetes and non-alcoholic fatty liver disease [10–15]. Compared with germ-free mice, conventionally raised mice were more prone to obesity and insulin resistance [10]. In human studies, it also has shown that gut microbiota composition differs between obese and lean subjects [11]. Recent metagenome-wide association studies showed that patients with type 2 diabetes have an increase in the abundance of Lactobacillus species and decreases in the abundance of Clostridium species [12, 13]. Thus, reshaping the gut microbiome may be a new direction for the prevention and treatment of diabetes in human beings. Currently the published evidences of the treatment of metabolic diseases with probiotics are limited, and the results are inconsistent [16–19]. Some but not all trials suggest that probiotics consumption may improve blood glucose level and antioxidant status in type 2 diabetic patients [16]. Two trials showed that probiotics intervention only improved the lipid metabolism but not blood glucose in patients with diabetes or gestational diabetes mellitus [17, 18]. Only one trial explored the effects of probiotics administration on the outcomes of blood lipids and blood pressure in patients with prediabetes, but no data on the outcome of glucose metabolism [19]. In addition, the intervention period of those trials may be too short (4 to 8 weeks) to observe the effect of probiotics. To date there is no clinical trial to explore whether probiotics administration can reduce the risk of development of type 2 diabetes in patients with prediabetes.

Therefore, the purpose of this study is to investigate the efficacy and safety of probiotics administration in preventing the development of type 2 diabetes in subjects with IGT compared to placebo. In addition, we will determine probiotics administration improve insulin sensitive and metabolic variables. The secondary outcome measures include body composition, biochemical variables and the safety of probiotics.

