### Sample size calculations

We will aim to recruit 100 subjects in each arm of the trial. Assuming a rate of 35 % developing diabetes in placebo group in China [20, 21], a type I error of 0.05 with two-sided, we have 80 % power to detect a 14 % difference in probiotics group at 2 year follow-up (accounting for our primary outcomes).

Considering a dropout rate of 10 %, the sample size for enrolled patients will rise up to 220 for all patients.

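### The only stated reporting rule covers adverse events judged possibly related to probiotics, so a causality judgement filters events before safety is compared with placebo

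*Protocol article*

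**What the plan says.** The section on reporting of adverse events has two sentences. The first gives the reporting rule: "We will report adverse events that might be reasonably related to probiotics". The second gives the collection rule: "Adverse events are collected from time of signature of informed consent throughout the treatment period". The collection rule has no relatedness limit; the reporting rule has one.

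Safety is part of what the trial sets out to show. The abstract says "we aim to explore the efficacy and safety of probiotics intervention in preventing type 2 diabetes in Chinese patients with impaired glucose tolerance". The Background makes the aim comparative, namely to "investigate the efficacy and safety of probiotics administration in preventing the development of type 2 diabetes in subjects with IGT compared to placebo". The secondary outcomes include "iv) the safety assessment of probiotics".

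On who would judge relatedness, the Randomization section says "Research staff and participants remain blind to the allocated treatment group", and the Interventions section keeps the allocation key with a third party until the analysis is finished. The article does not say who makes the judgement or by what criteria.

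**The concern.** In a randomised, blinded, placebo-controlled trial, the difference between arms in all events is the evidence on whether the product causes harm. A reporting rule that first asks whether each event might be due to the product reverses that order. Causality is settled event by event, on opinion, and only what survives is compared.

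At stake is the safety conclusion of a 24-month trial of a live three-strain product. An excess of a kind of event that the assessors do not connect with probiotics would be thinned out, or absent, in the reported comparison. The trial would still be read as evidence on safety against placebo. The primary outcome is not affected.

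**Working it through.** The plan states no figure on this point, so there is none to reproduce. The check is a comparison of sections, followed by an illustration of scale.

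**Step 1: does any other section lift the filter?**

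- *Abstract, Background and Discussion:* safety is named as an aim or purpose; no reporting rule.
- *Secondary outcomes:* safety is listed; no definition of which events count.
- *Follow-up visits:* the visits serve partly to detect adverse events. This concerns collection, not reporting.
- *Statistical methods:* general rules on intention-to-treat, differences with 95% confidence intervals, and chi-square tests during follow-up. Adverse events are not named. The secondary outcomes listed for the mixed models are "the difference of the changes of blood glucose, lipid profile and insulin sensitivity, body weight, waist circumference, abundance of bacteria, levels of LPS and GLP-1"; safety is not among them.
- *Reporting of adverse events:* open collection, reporting limited by possible relatedness.

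No section promises that all adverse events, or all serious ones, will be reported by arm.

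**Step 2: how much could a blinded filter hide?**

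Inputs from the article: arm size ("We will aim to recruit 100 subjects in each arm of the trial") and the two-sided 5% level (Statistical methods). Assumed, because the article gives no such figures: the true proportions with an event, p1 on placebo and p2 on probiotics, and the share s of events judged related. The share is taken as equal in both arms because the judgement is blind, with one event per affected participant for simplicity.

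The visible proportions are s·p1 and s·p2, so the visible difference is s·(p2 − p1). With q1 = s·p1, q2 = s·p2, q̄ their mean and n = 100:

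power = Φ{ [ (q2 − q1) − 1.96·√(2q̄(1 − q̄)/n) ] / √( [q1(1 − q1) + q2(1 − q2)]/n ) }

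For 30% against 50% with all events shown (s = 1): √(2 × 0.4 × 0.6/100) = 0.0693 and √((0.21 + 0.25)/100) = 0.0678. Then (0.20 − 1.96 × 0.0693)/0.0678 = 0.95, which gives power 83%.

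For the same rates with s = 0.5, the visible proportions are 15% and 25%: √(2 × 0.2 × 0.8/100) = 0.0566 and √((0.1275 + 0.1875)/100) = 0.0561. Then (0.10 − 1.96 × 0.0566)/0.0561 = −0.19, which gives power 42%.

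| Assumed true rates | Share judged related | Visible difference (points) | Power |
|---|---|---|---|
| 30% v 50% | 100% | 20 | 83% |
| 30% v 50% | 75% | 15 | 64% |
| 30% v 50% | 50% | 10 | 42% |
| 30% v 50% | 25% | 5 | 22% |
| 20% v 35% | 100% | 15 | 66% |
| 20% v 35% | 50% | 7.5 | 34% |
| 20% v 35% | 25% | 3.75 | 18% |

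A filter that treats both arms alike still shrinks a real excess in proportion to s, and power falls with it. With no difference between the arms (p1 = p2), the visible difference stays at zero for any s, so under these assumptions the filter costs sensitivity without creating a false difference.

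**The case against.** The strongest reply is that the sentence does not exclude anything. It says what will be reported and is silent on the rest. *Report* could also mean passing on suspected reactions during the trial rather than tabulating results: the section names no table, arm or comparison, and it stands between the statistical methods and the ethics section. The general rules under Statistical methods could cover a safety comparison and carry no relatedness limit. Layout of safety tables is normally left to an analysis plan.

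Part of this stands. The exclusion is an inference from a sentence that names one class of events, and the other meaning of *report* cannot be ruled out. But the article gives no other rule for adverse events, and Statistical methods does not mention them. If all events were meant to be reported, the qualifier has no purpose. Nor is this a detail left to another document: the article itself states the limit.

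A reader might also infer three stronger things that the article does not support.

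- *That the criterion means nothing in the placebo arm.* Staff are blind, so the same question is put to events in both arms while the blind holds.
- *That every unexpected harm is removed.* Relatedness is not expectedness. An unforeseen event can be judged possibly related, and the threshold is worded inclusively.
- *That the arms are compared with bias.* Blinded judgement argues against differential filtering.

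**Conclusion.** The point holds as a defect in a stated rule. Read as written, the reporting sentence removes events judged unrelated from the safety comparison with placebo that the article names as an aim and lists as a secondary outcome. The consequence is lost events and lost sensitivity, greatest for harms that assessors do not suspect to be related.

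The size cannot be established from the article, which gives neither event rates nor the share likely to be judged related. The figures above illustrate the mechanism under assumed rates, an equal retained share in both arms and 100 per arm; they do not predict this trial's results. A reader might conclude that safety data will be lost for good. The article does not support that: collection is unrestricted, so the fault lies in reporting and can be put right from the data in hand. The change should be made, but it does not threaten the primary result.

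**What to change.** Replace the reporting sentence with:

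*All collected adverse events and serious adverse events will be reported and compared by randomised arm regardless of judged causality; relatedness, judged blind, is shown as a supplementary breakdown.*

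If the present sentence was meant for onward reporting of suspected reactions during the trial, say so and keep it as a separate rule beside the new one.

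The cost is a longer safety table. No further data collection, visit or change to the primary analysis is needed.
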